## **Muscle and Strength Measurements**

A sequence of three physiological measures will be undertaken:

***Time up and Go:*** The participant will start in a seated position.

The participant will stand up upon therapist's command, walk 3 meters, turn around, walk back to the chair and sits down.

The time will stop when the participant is seated.

The subject can use an assistive device. If the assistive device is used, it will be documented.

**NOTE:** A practice trial will be completed before the timed trial

***30 seconds sit to stand.*** The 30-Second Chair Test is administered using a folding chair without arms, with a seat height of 17 inches (43.2 cm). The chair, with rubber tips on the legs, is placed against a wall to prevent it from moving.

The participant is seated in the middle of the chair, back straight; feet approximately shoulder width apart and placed on the floor at an angle slightly back from the knees, with one foot

slightly in front of the other to help maintain balance. Arms are crossed at the wrists and held against the chest.

Demonstrate the task both slowly and quickly.

Have the participant practice a repetition or 2 before completing the test.

If a participant must use their arms to complete the test, they are scored 0.

The participant is encouraged to complete as many full stands as possible within 30 seconds.

The participant is instructed to fully sit between each stand.

While monitoring the participant's performance to ensure proper form, the tester silently counts the completion of each correct stand. The score is the total number of stands within 30 seconds (more than halfway up at the end of 30 seconds counts as a full stand). Incorrectly executed stands are not counted.

The 30-second chair stand involves recording the number of stands a person can complete in 30 seconds rather than the amount of time it takes to complete a pre-determined number of repetitions.

**Muscle strength Assessment:** Isokinetic testing will be done at 60 and 180 degrees of flexion as done in previous study (103) and participant will be in sitting position with hips and knees strapped to keep the position standardised.

### **Pressure Pain threshold (PPT)**

PPT is a non-invasive test during which the sensitivities of the nerves are assessed by recording the smallest force applied to the skin. When this force by the surface area of the skin is applied (pressure), this will be felt as mild, temporary pain and recorded. The pressure probe used consists of a rod with an end the size of a 5p piece, mounted in a handheld device connected to a computer. The force with which the probe is pressed onto the skin is gradually increased until the participant indicates (by pressing a button) that the sensation has changed from pressure to pain. The probe is then automatically immediately taken off the skin. The probe will be used on knees, and proximal shins using a standardised protocol used in other studies within the Pain Centre. Each region will be tested three times with short rest periods between. The participants will be familiarised with the test before it is administered so that they know what to expect and how to respond.

### **Continuous Pain Modulation (CPM)**

CPM will be done along with PPT testing. The reference point for PPT testing will be 3cm medial to patella on the most painful knee. Verbal instructions will be given to the participant. The Numerical Rating Scale (NRS) target will be  $\geq 4$  out of 10 from the cuff pressure. Staff/clinician will wrap 7.5cm wide tourniquet cuff around the contralateral arm to the knee being tested. The lower rim of tourniquet cuff will be kept 3cm proximal to cubital fossa. Systolic pressure will be set to 270mmHg. After target pressure is achieved, the participant will be asked to rate sensation in the arm from 0-10. The participant will be asked to make hand grip  $\geq 10$  times until NRS of 4 will be reached. NRS rating will be asked every five hand grips. Once NRS of 4 will be achieved, the probe of algometer will be applied in the same manner as before to knee test site (during PPT testing). Once the participant presses the button, the probe will be withdrawn, and cuff will be released from the elbow. Participants will be advised to wait until cuff evoked pain subsides before re-test, and a minimum of 1 minute should be spared. PPT test will be repeated again (without the cuff now). Their difference in PPT score (with conditioning – without conditioning) will establish the CPM effects. Positive value predicts efficient and negative value predicts in-effective CPM.

### **Temporal Summation (TS)**

The mechanical temporal summation is a non-invasive test during which repetitive mechanical stimulation is applied over a short period to get their augmented response. Increased pain response to a repeated mechanical stimulus may indicate enhanced central sensitisation. The test site will be a suprapatellar region (5 cm proximal from the central part of patella).

A 256mN weighted pinprick stimulator will be used and applied perpendicular to the skin of suprapatellar region of affected knee (5cm proximal from the centre of patella). The participant

will be asked to rate the pain or sharpness they experience from 0-100 where 0 indicates no pain or sharpness and 100 indicates the most intense pain or sharpness imaginable. Numerical Rating Scale (NRS) with verbal descriptors will be used. The response of the participant will be recorded. The same stimulator at the same site will be applied ten times repeatedly at a rate of 1/second. The size of the site would be kept approximately 1 cm square. At the end of the series of 10 pinpricks, the participant will be asked to rate the pain or sharpness which they experience averaged over the whole series of 10 stimuli using the same NRS. The mechanical temporal summation reading will be calculated as the difference between two ratings which is second rating minus the first rating.

### **Compliance**

Compliance will be judged by the online participation of individuals to follow their exercises and by the attendance of two face to face sessions. E-mail prompts are routinely sent out reminding individuals of their exercises. Furthermore, individuals will be given a contact number to contact us as to if they have any query.

### **Criteria for terminating the study**

As the study involves two assessments only and does not involve investigational medicinal products or medical devices it is not envisaged that circumstances will arise that require termination of this study.

### **Radiographic Evaluation**

Tibiofemoral and patellofemoral radiographs will be taken using a standardised protocol (standing posterior-anterior (PA) and skyline views) and will be scored by a single experienced observer. A Perspex Rosenberg template with lead beads is used for the standing PA view to standardising the degree of knee flexion, foot rotation and magnification (108). PA radiographs are taken with the participant facing the x-ray tube while standing on the Rosenberg jig and leaning forwards with their thighs touching the anterior aspect of the jig, the x-ray beams passing from the posterior aspect through to the anterior aspect of the knee. Variable jigs are used for the skyline view to obtaining 30° of knee flexion with the participant lying in a reclined supine position on a couch

Grading of radiographs for changes of OA will be based on the Kellgren and Lawrence (K/L) score (109, 110).

### **Radiation Exposure**

This study involves exposure to a very small amount of additional radiation. As part of everyday living, everyone is exposed to naturally occurring background radiation. The effective dose for this study has been estimated to be roughly equivalent to half a day of average background radiation in the UK. At this dose level, no harmful effects of radiation have been demonstrated as any effect would be too small to measure. The risk is believed to be minimal.

The following effective dose figures have been estimated using PCXMC 2.0 and either exposure factors & radiographic technique or audit data on DAPs/examination.

- Semi-flexed weight-bearing view 0.62µSv
- Skyline view (both knees) 1.0 µSv (One knee) 0.5 µSv

If a participant received the highest doses, then this would give  $\approx 1.6\mu\text{SV}$  for all exposures. Bearing in mind that practice varies between sites, other dose data suggests that doses may vary by a factor of two. Therefore we could assume a maximum of  $3\mu\text{SV}$  per participant from research exposures.

## **Transport and Storage of the Tissues**

The sample will be stored at the premises which belongs to University of Nottingham. Whole blood (5ml) samples will be stored in a refrigerator (at  $-20^{\circ}\text{C}$ ). Remaining blood (10ml) will be centrifuged as soon after venesection as possible and the serum stored, with the urine, at  $-80^{\circ}\text{C}$  within freezers in University of Nottingham premises at the Clinical Sciences Building (CSB), City Hospital for future metabolomic studies. Excess samples (serum, urine and faeces) that remain after the study analyses have been undertaken will remain stored within the CSB for possible future research studies related to OA and/or pain provided that participants are agreeable and sign the optional clause on the consent form. These CSB facilities come within the remit of the Research Tissue Bank ([name] Licence Number 12265) where participants do not agree to the future use of the samples they will be destroyed in accordance with the Human Tissue Act, 2004.

Samples will be stored in the linked anonymised format in the CSB and labelled using a randomly generated unique participant identifier to permit accurate linkage to clinical data and the consent form. The master database will be held by the CI in an encrypted password file.

## **Laboratory Analysis**

Whole blood may be sent to a specialist company for processing using standard protocols. Bacterial DNA will be extracted from faecal samples to identify bacterial lineages associated with pain and inflammation in OA. Faecal samples will be stored till we have all the samples (as this is optional) and then we will send it to the laboratory. Similarly, biochemical analyses may be undertaken by other academic or commercial groups. Such investigations will be undertaken on anonymised samples under usual Material Transfer Agreement arrangements. Storage of these tissues will be managed, transported and handled according to SOP HTMG 004. Companies which will be used for the analysis should process the samples within seven days upon receipt or companies with HTA licence will be considered.

## **STATISTICS**

### **Methods**

Associate [name] [name] will oversee the statistical analyses. The data will be entered into MS Access and analysed using SPSS (Statistical Packages for Social Scientists, version 19).

The results of the study will be available to the study management group. All data will be stored in Academic Rheumatology and will be backed up on the University of Nottingham servers.

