### **Randomization and Blinding**

Participants will undergo computer-generated stratified randomisation by a statistician at Academic Rheumatology using the <https://sealedenvelope.com/> software. Generation of a randomisation schedule will include obtaining the random numbers and assigning random numbers to each subject under the specific treatment conditions. Participants will be equally allocated between treatment arms with at least n=67 per arm.

Masking: Not applicable, the study is not double-blinded as participants will find out their allocated group, however, the examiner will be blinded to the intervention.

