### **Study Management**

The study will be managed in Academic Rheumatology, Clinical Sciences Building by the Research Manager under the supervision of the Chief Investigator who has overall responsibility for the study and shall oversee all study management.

The study management group will meet regularly and have documented quarterly meetings from the start of the study. The group will also monitor and supervise the progress of the study and advice on recruitment rate and unforeseen logistical issues to ensure that its objectives are achieved.

The data custodian will be CI who will also have overall responsibility for the study and shall oversee all study management.

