## **Duration of the Study and Participant Involvement**

### **Study Duration and Schedule of Events:**

The trial is expected to start in spring 2018 (May – June 2018), and enrolment will end in the late summer of 2020. After about two months from the end of recruitment, all data will be collected. Data analysis will be performed by a PhD student supervised by CI.

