## **ADVERSE EVENTS**

Increase in the knee, hip or back pain are possible adverse effects (106). One case of raised hypertension has been reported by a previous study (111).

Participants will be asked to contact the study site immediately in the event of any serious adverse event. Any adverse event will be recorded and closely monitored until resolution, stabilisation or until it has been shown that the study treatment / intervention is not the cause. Participants can contact physiotherapists (SG) if there is any adverse event. The CI shall be informed immediately of any serious adverse events and shall determine seriousness and causality in conjunction with any treating medical practitioners.

Any serious adverse event (s) related to this study will be recorded and reported to the REC as part of annual reports. Unexpected serious adverse events will be reported within timeframes to the REC and CI will be responsible for all adverse event reporting.

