### **Randomisation**

Participants will undergo computer-generated stratified randomisation by a statistician at Academic Rheumatology using the <https://sealedenvelope.com/> software. Generation of a randomisation schedule will include obtaining the random numbers and assigning random numbers to each subject under the specific treatment conditions. Participants will be equally allocated between treatment arms with at least n=67 per arm. As the online system will be used for randomisation, therefore, code break will be kept online, and the research manager will be responsible for keeping a track of it.

As per cohort multiple randomised controlled trial design mentioned by another study (54), individuals will have an assessment to establish their suitability for this study and once that has been established, we will randomise them into control group and interventional group. At this occasion, individuals will find out that they belong to one group or the other and hence blinding is not possible. Because the lack of masking might affect the motivation of participants randomised into the control arm, individuals in the control arm will be offered access to the web-based exercise programme after the six weeks of the study, if they wish to use it to avoid a placebo effect in this group. Blinding such interventional studies are difficult to achieve as participants will establish as to in which group they are in, however, the examiner will be blinded to the intervention.

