### **Analysis methods**

The distribution for each difference score will be evaluated. If the score follows an approximately normal distribution with no apparent outliers, between group differences will be analysed through ANOVA with adjustment for baseline scores (ANCOVA). Due to the randomisation, no systematic differences between groups are expected and hence no control for further “confounding” will be performed. Results for the between group comparison will be presented as “difference in mean difference” with accompanying 95% confidence intervals.

Within group differences from baseline to follow up will be evaluated through pre-post mean difference with accompanying 95% CI. Differences/changes with confidence intervals not covering “0” will be considered statistically significant. Standardised effect sizes (Cohen’s D) will be computed (mean difference/baseline SD).

If the difference scores clearly deviate from a normal/symmetric distribution, the comparisons will instead be performed through non-parametric analyses. For the

between group comparisons, Mann-Whitney test will be applied and for the within group comparison, Wilcoxon signed rank test will be used. Results will be presented as median scores (IQR) and p-values. No adjustment for baseline scores will be performed, as the non-parametric tests do not allow for this.

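### Nothing withholds trial arm from the people who analyse the data, while the SAP leaves the choice of primary test, and the actigraphy sleep variable, to undefined judgement

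*Combined protocol and SAP*

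**What the plan says.** **Masking.** Protocol, Randomization and Blinding: participants learn their group, but "the examiner will be blinded to the intervention". The protocol's Study Regimen and SAP Section 3 (Randomisation) repeat this. No one else is masked anywhere.

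**Who analyses.** Protocol, Study Duration and Schedule of Events: "Data analysis will be performed by a PhD student supervised by CI". Protocol, Statistics – Methods: an Associate, whose further details are removed, "will oversee the statistical analyses. The data will be entered into MS Access and analysed using SPSS". Protocol, Study Management: "The data custodian will be CI who will also have overall responsibility for the study".

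**Who holds the code.** The allocation code is kept online. SAP Section 3 (Randomisation): "the research manager will be responsible for keeping a track of it". Study Management places the research manager under the CI's supervision.

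**What is left to judgement.** SAP Section 6 (Analysis methods) uses ANCOVA on the change score if that score has an "approximately normal distribution with no apparent outliers". If the score departs clearly from a normal or symmetric shape, Mann-Whitney replaces it and the baseline adjustment is dropped. Neither condition has a threshold, a test or a named decision-maker. The same rule covers NRS pain and the secondary outcomes. For sleep, SAP Section 6 (Outcome variables) names the ActTrust device but no derived variable, scoring window or valid-night rule.

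**The concern.** The primary outcome is reported by participants who know their arm, so masking the examiner does not protect it. The next point at which knowledge of arm could enter is the analysis. Someone must look at the change scores, decide whether they are normal enough and free enough of outliers, and so decide which of two tests is the primary one. If arm is in the file, both results can be seen before that decision is made. Nobody need intend anything for the more favourable route to look like the more reasonable one. What is at stake is a somewhat higher chance of a false claim for the web programme, and a report that cannot show the choice was made blind. The undefined sleep variable has the same weakness on a secondary outcome.

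**Working it through.** **1. The plan's own figure.** The concern rests on no stated figure, but the power statement shows which alpha the plan uses. Inputs (SAP, Sample size): effect 0.49 SD, 60 per arm, alpha 0.05. Power = Φ(0.49 × √(60/2) − 1.960) = Φ(2.684 − 1.960) = Φ(0.724) = 76.5%; the t-test version gives 75.9%. Both agree with the stated 75%. A one-sided alpha would give 85.1%, so the plan is two-sided at 0.05.

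**2. The passages side by side.**

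| Question | Answer in the documents |
|---|---|
| Who is masked? | The examiner only |
| Who reports the primary outcome? | Participants who know their arm |
| Who analyses? | A PhD student supervised by the CI, with an Associate overseeing |
| Is the overseer independent of the study team? | Not shown; details removed |
| Coded arms, blind data review, or lock before arms are revealed? | Not provided for |
| Who decides between ANCOVA and Mann-Whitney, and on what threshold? | Not stated |

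**3. How much room the test choice leaves.** Null simulation restricted to the two routes that SAP Section 6 permits.

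From the documents:
- 105 participants completed both visits (SAP Section 3, Timing of outcome assessments).
- NRS is scored 0–10.
- The SD implied by the sample-size section is 1.2/0.49 = 2.45.

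Assumed:
- a 53/52 split, since completers are not given by arm;
- scores rounded to whole numbers;
- a baseline to follow-up correlation of 0.4–0.6;
- no true effect.

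Route 1 is change = a + b·arm + c·baseline, testing b = 0. Route 2 is Mann-Whitney on the change scores. Two rates are compared: P(route 1 gives p < 0.05), and P(route 1 or route 2 gives p < 0.05). The second describes an analyst who always takes the better of the two.

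| | Two-sided | Favouring web arm |
|---|---|---|
| ANCOVA fixed in advance | about 5% | about 2.5–3% |
| Better of the two permitted tests | about 7–8% | 3.4–4.4% |

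The ranges cover repeated runs of 4,000 to 5,000 null trials per correlation. At 5,000 trials the Monte Carlo standard error of a 5% rate is √(0.05 × 0.95/5,000) = 0.3 points. In one run of 5,000 the web-favouring rate was 3.9–4.1%, against 2.7–2.9% for ANCOVA alone, an excess of 1.2 points.

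**4. Sleep.** With no variable named, the number of candidates is unknown. If 3, 5 or 8 independent measures were tried, the chance of at least one p < 0.05 is 1 − 0.95^k = 14%, 23% or 34%. Both k and independence are assumptions; positively correlated measures would give less.

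**The case against.** The strongest reply is that the root cause is the vague switch rule, not the missing masking. Fix ANCOVA as the primary test and little discretion remains on the primary outcome. That is right. It is why the fix offers this as an alternative, and why masking should not be called the main protection still available. Masking still adds something. The SAP reports the stop of 19 March 2020 and the 105 completers, so at least that text was written after the trial stopped, and a rule tightened now could itself be chosen with arm in view. That timing does not show that anyone had seen outcomes by arm.

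It can also be said that the lack of analyst masking is inferred from silence. That is so, but a plan that specifies examiner masking repeatedly and analyst masking nowhere does not provide for it.

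Several stronger readings are tempting, and the documents do not support them:

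- *The analysis is wholly inside the study team under the CI.* The CI's supervision of the analyst is stated, but a separate Associate oversees the analyses. That person's independence can be neither affirmed nor denied.
- *The CI's role in serious adverse events adds to the problem.* It has no bearing on outlier, distribution or sleep decisions. It is shared, since the CI "shall determine seriousness and causality in conjunction with any treating medical practitioners", and SAP Section 4 plans no safety analysis.
- *The non-compliance count is another exposed judgement.* Adherence is defined from activities the platform distributes, so it concerns the web programme. It is reported as a count and does not define the ITT comparison.
- *False positives could reach 9–10%.* That needs extra analyses that delete outlying changes. The SAP authorises no such deletion.

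Finally, SAP Section 4 treats every non-primary analysis as exploratory and reads it by general pattern, so the sleep gap carries less weight.

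**Conclusion.** The concern holds in a limited form. The plan lets the primary test be chosen by people from whom arm is not withheld, on criteria it does not define. For the two tests the SAP permits, the upper bound is about 7–8% two-sided against about 5%, and 3.4–4.4% favouring the web arm against about 2.5–3%. This rests on the assumed 53/52 split, correlations of 0.4–0.6 and deliberate choice of the better result every time, so it is a ceiling and not a forecast. The documents show only that the choice could be made with arm visible. The sleep gap is real but touches a secondary, exploratory outcome. The point merits action because the remedy is cheap, not because the expected bias is large.

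**What to change.** Amend the protocol (Study Duration and Schedule of Events; Statistics – Methods) and SAP Section 6 as follows.

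1. The research manager, who already tracks the code, releases the analysis file without the arm variable. Platform adherence data, which would reveal the web arm, stay in a separate file.
2. The distribution judgement and the actigraphy scoring are made on data pooled across arms and signed off by the overseer of the analyses. Alternatively, ANCOVA is fixed as the primary test and only the actigraphy scoring needs this step.
3. The analysis is run with arms labelled A and B.
4. Arms are named only after the primary result is signed off.
5. If arms have already been seen, the report says so.

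The cost is one recoding step and a sign-off by existing staff. Pooled distribution checks are slightly less informative than per-arm checks. Two limits remain. The research manager works under the CI, who is also data custodian, so the sign-off belongs with the overseer. And masking the analysis does nothing about participants reporting pain in knowledge of their arm.
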